### Hypothesis

We hypothesize that this integrated, explainable AI approach will outperform conventional monitoring strategies, improve risk stratification for CSPH, and enhance clinician adherence to evidence-based care pathways, ultimately reducing symptom burden and preventing complications in patients with PBC.

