### Outcomes

The primary outcome for the first aim will be the performance of the AIm-PBC disease activity index compared to conventional monitoring strategies. This will be assessed through its calibration against established risk scores such as UK-PBC and GLOBE [22,23], as well as its responsiveness to clinically meaningful changes in disease activity. The ability of the integrated symptom indexes to correlate with biochemical progression or regression will also be evaluated, providing insights into whether the inclusion of PROs enhances the sensitivity of disease monitoring. Explainability will be measured via the interpretability of SHAP-based visualizations and their perceived clinical utility during clinician evaluations.

For the second aim, the primary outcome will be the discriminatory ability of the multi-signal predictive model to identify patients at high risk of CSPH and early complications such as variceal hemorrhage or ascites. This will be quantified using the area under the receiver operating characteristic curve (AUROC), with additional measures of calibration and clinical utility assessed through decision curve analysis and net reclassification improvement. Comparative analyses will determine whether the composite model outperforms single-modality rules and consensus criteria such as Baveno VII, and subgroup analyses will explore performance consistency across patients with AIH overlap and MASH.

For the third aim, the primary outcome will be the effectiveness and usability of the EHR-integrated CDS prototype. Effectiveness will be measured via improvements in clinician adherence to guideline-concordant care pathways, including pruritus management, bone health interventions, and risk-based endoscopy referrals. Usability will be assessed using the System Usability Scale, with a target score of 70 or higher, and cognitive load will be evaluated using the NASA-Task Load Index. Clinician trust in the AI system will be measured through the AI trust scale, whereas decision accuracy and decision time will be compared between CDS-assisted and usual care conditions during the randomized crossover simulation. Feasibility indicators, including recruitment and completion rates, will be monitored during the pragmatic pilot phase.

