### Statistical Analysis

For the first aim, longitudinal PROs and biochemical markers will be analyzed using mixed-effects models to account for within-subject correlation and repeated measures over time. These models will assess the responsiveness of integrated symptom indexes to changes in biochemical progression or regression, whereas calibration of the AIm-PBC disease activity index will be evaluated against established risk scores such as UK-PBC and GLOBE using the calibration slope, intercept, and Brier score. Discrimination will be quantified through the AUROC, and visualizations of SHAP values will be examined to confirm clinical interpretability.

For the second aim, the predictive model for CSPH complications will be developed using gradient-boosted ensemble algorithms chosen for their robustness in handling heterogeneous data. Model performance will be assessed through the AUROC for discrimination and calibration plots for agreement between predicted and observed outcomes. Clinical utility will be evaluated using decision curve analysis and net reclassification improvement to determine whether the composite model offers meaningful improvement over existing criteria. Comparative analyses will use DeLong tests to assess differences in AUROC between models, and subgroup analyses will be conducted to evaluate fairness and consistency across patients with AIH overlap and MASH. Ablation studies will quantify the incremental value of individual predictors, particularly SSM, by systematically removing variables and observing changes in performance.

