## Results

At the time of manuscript submission, this protocol had not yet begun participant recruitment or data analysis. No participants had been recruited. The study did not receive external funding; therefore, no funding date is applicable. Data collection is projected to begin after institutional review board approval and ClinicalTrials.gov registration, with retrospective data extraction and prospective observational data collection expected to occur over approximately 24 months. The clinician-level randomized crossover simulation and pragmatic pilot implementation phases are expected to occur after model development and validation are completed. Data analysis will begin after completion of the relevant data collection phases. The main study findings are expected to be submitted for publication in summer 2029.

The integrated disease activity index is expected to show strong calibration with established prognostic scores and greater responsiveness to clinically meaningful changes, whereas the inclusion of PROs will provide a more comprehensive view of symptom burden. The predictive model is expected to achieve an AUROC of at least 0.85 for identifying CSPH and deliver a net reclassification improvement of 10% or more over Baveno VII criteria, reducing unnecessary endoscopies without compromising safety. Finally, the CDS prototype is expected to improve clinician adherence to guideline-concordant care pathways, reduce decision time, and achieve high usability and trust scores during the simulation and pilot phases.

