### Comparison With Prior Work

Previous efforts in PBC management have focused primarily on biochemical monitoring and static risk scores such as UK-PBC and GLOBE, which do not account for dynamic symptom burden or integrate noninvasive imaging markers. Similarly, consensus criteria provide useful surrogates for portal hypertension but lack individualized predictive capability. Machine learning models have shown promise in chronic liver disease, yet most operate as opaque systems, limiting clinician trust and adoption. This study builds on these foundations by introducing an explainable, multi-signal approach that combines objective and patient-reported data, integrates noninvasive imaging, and operationalizes insights through EHR-based decision support.

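### The calibration part of the Aim 1 primary outcome takes UK-PBC and GLOBE predictions as its reference and names no observed event, so it measures agreement with those scores and cannot show better calibration than they have.

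*Protocol article*

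**What the plan says.** The Outcomes section defines the Aim 1 primary outcome as "performance of the AIm-PBC disease activity index compared to conventional monitoring strategies". It gives two parts. The first is calibration: "This will be assessed through its calibration against established risk scores such as UK-PBC and GLOBE". The second follows in the same sentence: "as well as its responsiveness to clinically meaningful changes in disease activity".

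Statistical Analysis repeats the first part and adds the metrics: the "disease activity index will be evaluated against established risk scores such as UK-PBC and GLOBE using the calibration slope, intercept, and Brier score". It then adds an AUROC for Aim 1 without naming the binary outcome.

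The Results section, which sets out expectations, says the index is "expected to show strong calibration with established prognostic scores and greater responsiveness to clinically meaningful changes". Principal Results, in the Discussion, goes further and anticipates an index that is both more responsive and better calibrated than conventional monitoring.

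The Hypothesis is that the "integrated, explainable AI approach will outperform conventional monitoring strategies". Comparison With Prior Work describes the existing tools as "static risk scores such as UK-PBC and GLOBE, which do not account for dynamic symptom burden or integrate noninvasive imaging markers".

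**The concern.** Calibration slope, calibration intercept and Brier score compare predicted probabilities with events that did or did not happen. A risk score is not such an event. With a score as the reference, the metrics describe how closely one prediction tracks another.

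That conflicts with the purpose of the index. It is built to add symptoms and elastography to what UK-PBC and GLOBE use. If those scores are the standard, a departure from them caused by useful new information is recorded as error in the same way as a departure caused by noise. An index that merely reproduced a score would pass perfectly and would also inherit any miscalibration of that score unseen.

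At stake is one component of the primary outcome of one of three aims, together with the claim of better calibration. No comparator can be beaten on agreement with itself.

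**Working it through.** The article gives no numerical target, power statement or event rate for Aim 1 calibration, so there is no stated figure to reproduce. The check has four steps.

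**1. The sections side by side.**

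| Place | Reference for calibration |
|---|---|
| Outcomes, Aim 1 | UK-PBC and GLOBE |
| Statistical Analysis, Aim 1 | UK-PBC and GLOBE, by slope, intercept and Brier score |
| Results, Aim 1 expectation | the established scores |
| Statistical Analysis, Aim 2 | observed outcomes |
| Principal Results | conventional monitoring, as a comparator to be bettered |

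The first three rows agree. The Aim 2 row shows that the usual reference is applied elsewhere in the same section. Data Collection tracks time to varices, ascites and encephalopathy over 24 months, so an observed reference exists in the study.

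**2. Algebra.** Work on the logit scale. Let the score have variance V. Let the index equal true risk, namely the score plus added information of variance kV that is uncorrelated with the score. The slope of score on index is covariance over variance of the index:

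slope = V / (V + kV) = 1 / (1 + k)

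- k = 0.25: 1/1.25 = 0.80
- k = 0.5: 1/1.5 = 0.67
- k = 1: 1/2 = 0.50

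A copy of the score has k = 0, hence slope 1, intercept 0 and squared difference 0. The values of k are assumptions; the article supplies none.

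**3. Simulation on assumed inputs.** N = 400,000. True risk is logistic in x1, seen by the existing score (log-odds 1.0 per SD), and x2, new information (log-odds 0.5 or 1.0 per SD, so k = 0.25 or 1). Event rates are 5%, 10% and 24%. The first two are assumed; the last borrows the lower CSPH prevalence from Sample Size and Power Considerations. Mean squared difference stands in for the Brier score when the reference is a score. Results at a 10% event rate, with a score that is itself calibrated:

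| x2 effect | Index | Slope v score | Mean logit gap v score | Squared difference v score | Slope v outcome | Brier v outcome | AUROC v outcome |
|---|---|---|---|---|---|---|---|
| 0.5 | copy | 1.00 | 0.00 | 0 | 1.00 | 0.0822 | 0.747 |
| 0.5 | true risk | 0.78 | 0.10 | 0.0024 | 1.00 | 0.0799 | 0.773 |
| 1.0 | copy | 1.00 | 0.00 | 0 | 1.00 | 0.0838 | 0.731 |
| 1.0 | true risk | 0.45 | 0.39 | 0.0089 | 1.00 | 0.0750 | 0.818 |

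Across the three event rates, the true-risk index has slope 0.77 to 0.79 (x2 = 0.5) or 0.43 to 0.47 (x2 = 1.0) against the score, and 1.00 to 1.01 against outcomes. If the score doubles the true odds, the copy still gets slope 1.00 and gap 0.00 against the score. Against outcomes its intercept is -0.69 (that is, -ln 2), which exposes the fault.

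**4. Where the algebra stops.** If the added part has covariance c with the score, the slope is (V + c) / (V + kV + 2c). Setting this to 1 gives c = -kV, which is possible for k up to 1 because |c| cannot exceed V√k. So an index can add information and still show slope 1. The squared difference still favours the copy: it is 0 for a copy and above 0 for any index that differs from the score.

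**The case against.** The strongest reply is that evaluating calibration against the scores means benchmarking it against theirs. The framing in Outcomes as a comparison with conventional monitoring and the superiority language in Principal Results both fit that reading, and the chosen metrics need events anyway. The circularity would then disappear, and the remaining gap would be an endpoint definition that an analysis plan (mentioned in Ethical Considerations) might supply. A reader should therefore not infer that the article rules out observed outcomes; no section does.

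This carries only part of the way. The Results section expects strong calibration with the scores, and Outcomes has calibration against them. Neither is the language of a comparator. The article fixes the reference and the metrics itself, so an analysis plan that follows it inherits the problem. On either reading, no observed outcome is named for the Aim 1 metrics or AUROC.

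Two further points stand. No section says the index is a probability, so mapping it to one moves it from disease activity towards prognosis and partly overlaps Aim 2. Events may also be scarce: Child-Pugh B and C are excluded and follow-up is 24 months. The 144 to 282 events in Sample Size and Power Considerations (600 × 0.24 and 600 × 0.47) derive from CSPH prevalence and are not new complications.

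**Conclusion.** The concern holds for the calibration component. Read literally and consistently across Outcomes, Statistical Analysis and Results, that component measures agreement with UK-PBC and GLOBE and cannot support a claim of better calibration. On the more generous reading, its metrics and the Aim 1 AUROC still lack the event they need.

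The slopes of 0.80 to 0.50 rest on an assumed k of 0.25 to 1 and on added information uncorrelated with the score. They illustrate direction and do not estimate the bias in this study.

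Two stronger conclusions might be drawn and are not supported. One is that the whole Aim 1 primary outcome fails: responsiveness is a separate part, and the calibration reference does not touch it. The other is that every piece of new information must lower the slope: step 4 of the working shows an exception, so the accurate word is generally.

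**What to change.** In Outcomes and in the Aim 1 paragraph of Statistical Analysis:

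1. Relabel agreement with UK-PBC and GLOBE as convergent validity and report it as such, for example by rank correlation. Align the expectation in Results.
2. Where calibration, Brier score or AUROC are claimed, map the index to the probability of an observed outcome already tracked in Data Collection. One option is a composite of varices, ascites or encephalopathy within 24 months. Report slope, intercept, Brier score and AUROC side by side for the index, UK-PBC and GLOBE on the same patients, recalibrating the two scores to that outcome and horizon where needed.
3. Leave responsiveness as a separate component.

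The cost is rewording, the choice of an outcome and horizon, and a modest extra analysis. Recruitment and analysis had not begun at submission, so the change can be made before any data are seen. Intervals may be wide and should be reported, and the overlap with Aim 2 should be acknowledged. If events prove too few, drop the claim of better calibration and rest Aim 1 on responsiveness and convergent validity.

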### Recruitment

Approximately 24 hepatology clinicians will be recruited for the clinician-level randomized crossover simulation. This sample size was selected pragmatically to provide sufficient clinician-level feedback on usability, cognitive workload, trust, and workflow integration while remaining feasible for a pilot implementation study. Eligible clinicians will include hepatologists, advanced practice clinicians, and hepatology trainees with clinical experience managing patients with PBC. Participants will be recruited from hepatology clinics affiliated with academic medical centers.

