### Randomization

Randomization will apply only to the implementation phase of the study during the clinician-level crossover simulation. Clinicians will be randomly assigned in a 1:1 ratio to 1 of 2 sequences: usual care followed by CDS-assisted care or CDS-assisted care followed by usual care. A computer-generated randomization schedule will be used to balance allocation between sequences and minimize allocation bias. The simulation will use standardized, deidentified cases rather than live clinical encounters.

To minimize learning and carryover effects, the 2 simulation periods will use distinct, nonoverlapping standardized cases matched in clinical complexity. A 1-week washout period will separate the 2 conditions, and case order will be varied within each period where feasible. Primary comparisons will be conducted within clinicians, allowing each participant to serve as their own control (Figure 2).

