For the third aim, implementation outcomes will be analyzed using both descriptive and inferential methods. Usability scores from the System Usability Scale (Multimedia Appendix 1), clinician trust scores from the AI trust scale adapted for AIm-PBC (Multimedia Appendix 2), and cognitive load measures from the National Aeronautics and Space Administration Task Load Index (Multimedia Appendix 3) will be summarized and compared between CDS-assisted and usual care conditions. Decision accuracy and decision time will be analyzed using 2-tailed paired *t* tests within the randomized crossover simulation, whereas clinician adherence to guideline-concordant care pathways will be evaluated using within-clinician comparisons across study phases. Feasibility indicators, such as recruitment and completion rates, will be reported as proportions with CIs. Qualitative debriefing interviews will be analyzed to explore clinician perceptions of usability, workflow integration, trust, and barriers to implementation (Multimedia Appendix 4). Fairness metrics, including AUROC parity gaps across demographic and clinical subgroups, will be calculated to ensure equitable performance of the CDS tool.

All analyses will be conducted using validated statistical software packages in R (R Foundation for Statistical Computing) and Python (Python Software Foundation), with significance thresholds set at a 2-sided α value of .05. Missing data will be addressed through multiple imputation techniques, and sensitivity analyses will be performed to confirm the robustness of the findings.

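### Paired t tests for decision accuracy and decision time leave the period and case-set difference in the error of the crossover, and let part of it into the CDS effect if the sequences end unequal

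*Protocol article*

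**What the plan says.** The Randomization section of the protocol article describes a two-sequence, two-period crossover (usual care then CDS, or the reverse): "Clinicians will be randomly assigned in a 1:1 ratio to 1 of 2 sequences". On the material used, "the 2 simulation periods will use distinct, nonoverlapping standardized cases matched in clinical complexity". On separation and order, "A 1-week washout period will separate the 2 conditions, and case order will be varied within each period where feasible". The comparison is paired by design: "Primary comparisons will be conducted within clinicians, allowing each participant to serve as their own control".

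On numbers, the Recruitment section states "Approximately 24 hepatology clinicians will be recruited for the clinician-level randomized crossover simulation" and adds "This sample size was selected pragmatically". It gives no effect size, SD or power.

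For the third aim, the Statistical Analysis section fixes the test: "Decision accuracy and decision time will be analyzed using 2-tailed paired" t tests, at a two-sided .05 level. No period, sequence or case-set term is named anywhere, and the sensitivity analyses are described only in general terms. The Outcomes section lists decision accuracy and decision time in its paragraph on the third aim's primary outcome.

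**The concern.** In this design the second period can differ from the first for two reasons unrelated to CDS: clinicians have had practice, and the cases are different ones. Matching on complexity does not ensure equal accuracy or equal time. Randomising to two sequences makes such a difference removable, because CDS falls in period 2 for one group and in period 1 for the other. A paired t test on CDS minus usual care does not use that. It pools both groups and reads the systematic gap between them as random variation.

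Two things are at stake. With equal sequences, precision is lost in a sample of about 24 that has no stated power. With unequal sequences, the estimated CDS effect is also shifted. This is the only randomised comparison in the study. The method is stated in the protocol and does not match the stated design, so the point is not a detail left to the analysis plan.

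**Working it through.** **Plan's own figure.** There is nothing to reproduce: 24 clinicians is a pragmatic number with no power calculation behind it.

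**Inputs from the protocol article.** About 24 clinicians (Recruitment); 1:1 to two sequences, different cases in each period (Randomization); paired t test, two-sided .05 (Statistical Analysis).

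**Assumptions not in the document.** Within-sequence SD of the within-clinician difference s = 1 (this sets the scale); true CDS effect tau = 0.6; period 2 minus period 1 difference d from 0 to 1; final splits of 12/12, 13/11, 12/10, 14/10 and 12/8.

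**Algebra.** Let D = CDS minus usual care for one clinician. Its mean is tau + d in the sequence usual care then CDS, and tau - d in the other.

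- Paired t test, estimate: the mean of D is tau + d(n1-n2)/(n1+n2), where n1 is the number in usual care then CDS. At 12/12 the second term is 0.
- Paired t test, error: at 12/12 the estimated variance of D is about s² + d², so the estimated SE is multiplied by about sqrt(1 + (d/s)²).
- With a period term: the estimate is the average of the two sequence means and the SE is (pooled SD/2) × sqrt(1/n1 + 1/n2), on n-2 degrees of freedom. The d cancels.

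**Balanced case, 12/12** (simulation, 60,000 replicates per scenario):

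| d (SD) | SE multiplier | Paired t, type I error | Paired t, power | Power with period term |
|---|---|---|---|---|
| 0 | 1.00 | 0.050 | 80.4% | 80.3% |
| 0.25 | sqrt(1.0625) = 1.03 | 0.043 | 78.7% | 80.3% |
| 0.5 | sqrt(1.25) = 1.12 | 0.029 | 73.1% | 80.3% |
| 0.75 | sqrt(1.5625) = 1.25 | 0.015 | 63.5% | 80.3% |
| 1.0 | sqrt(2) = 1.41 | 0.006 | 50.3% | 80.3% |

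A noncentral t calculation with variance s² + d² gives 0.804, 0.712 and 0.513 for d = 0, 0.5 and 1.0, and 0.802 with a period term (22 df). The small gaps to the simulation arise because that formula treats ±d as random noise, whereas it is a fixed shift within each sequence. Type I error drops for the same reason: at 12/12 the mean of D does not vary with d, but its estimated SE does.

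**Unequal sequences, shift in the CDS effect = d(n1-n2)/(n1+n2):**

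| Split | d = 0.5 SD | d = 1.0 SD |
|---|---|---|
| 13/11 | 0.5 × 2/24 = 0.042 | 0.083 |
| 12/10 | 0.5 × 2/22 = 0.045 | 0.091 |
| 14/10 | 0.5 × 4/24 = 0.083 | 0.167 |
| 12/8 | 0.5 × 4/20 = 0.100 | 0.200 |

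Exchanging n1 and n2 reverses the sign. In these scenarios the paired test's type I error stayed at or below about 0.05. With the period term the bias was 0 throughout and type I error was 0.050 to 0.052.

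**The case against.** The strongest reply is that the protocol works to keep both ingredients small. Cases are matched, there is a week between conditions, case order is varied where feasible, and "A computer-generated randomization schedule will be used to balance allocation between sequences and minimize allocation bias". With equal sequences the paired test is unbiased and conservative. The period difference is in no document; at 0.25 SD the loss is under two power points, and 1.0 SD would be large after matching. The 0.6 SD effect is also an assumption, and a pilot of pragmatic size makes no power claim that could fail. Multiple imputation is planned, so an analysis of unequal completers is not certain.

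Most of this stands, and it limits the size of the point. It does not remove it. The measures reduce d but do not show that it is zero. A schedule balances allocation, not completion, and the protocol treats completion as something to be measured. The term that would remove d is nearly free.

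A reader might infer more than the document supports:

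- That the test yields false positives. The calculation shows the opposite tendency.
- That the bias runs in the direction of learning. The sign depends on which sequence loses more clinicians, and case-set difficulty may offset learning.
- That adherence and NASA-TLX share the fault. Adherence is compared across study phases, and no specific test is fixed for NASA-TLX.
- That averaging over cases or skewed times makes the t test wrong. A t test on clinician-level summaries is legitimate, and aggregation and transformation can be left to the analysis plan.

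**Conclusion.** The point holds for decision accuracy and decision time: the stated test does not match the stated design. With equal sequences the harm is lost precision only. It is slight if d is about 0.25 SD (power about 79% instead of 80%), material at 0.5 SD (71-73%) and serious at 1.0 SD (50-51%). With unequal sequences the estimate and its confidence interval also shift, by 0.04 to 0.10 SD at d = 0.5 SD over the splits examined. All of this rests on the assumed d, the assumed 0.6 SD effect and the assumed splits. The document does not support calling the planned test invalid, or calling it biased when the sequences are equal. The change should be made because it protects against an unknown d at almost no cost.

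**What to change.** For decision accuracy and decision time, replace the paired t test with one of the following:

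- a linear mixed model with condition and period as fixed effects and clinician as a random effect; or
- a two-sample t test comparing clinician-level period differences (period 2 minus period 1) between the two sequences, with the difference in means halved to give the CDS effect.

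The Randomization section reads as one case set per period. Period and case set then coincide, and one period term removes both. State this explicitly. Add a separate case-set term only if the sets are counterbalanced across periods.

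Case-level modelling is optional. The change does not extend to adherence compared across study phases.

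The cost is a change of wording and one degree of freedom: at 12/12 with d = 0, power is 0.802 instead of 0.804. At 12/8 with d = 0 it is 70.2% instead of 72.2%, about 2 points.

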### Participant Timeline

Participants will enter the study and begin with baseline assessments, which include collection of demographic information, medical history, and initial laboratory values, as well as elastography measurements for liver and spleen stiffness. At this visit, participants will also be enrolled in the PRO system, with instructions for completing the WI-NRS and the PBC-40 questionnaires. These assessments will continue throughout the observation period to capture longitudinal symptom trajectories. The schedule of enrollment, interventions, and assessments is provided in Checklist 1.

Biochemical data will be collected at monthly intervals for the duration of the study, ensuring high-resolution monitoring of disease activity. Elastography will be repeated at predefined intervals, typically every 6 to 12 months or as clinically indicated, to track changes in liver and spleen stiffness over time. Clinical outcomes such as the development of varices, ascites, or hepatic encephalopathy will be monitored continuously through routine clinical care and documented in the study database.

For participants involved in the implementation phase, the timeline includes a randomized crossover simulation in which clinicians will manage deidentified cases under 2 conditions: usual care and CDS-assisted care. This simulation will occur after the development and validation phases are complete. Following the simulation, a pragmatic pilot will be conducted in real-world hepatology clinics, where the CDS tool will be integrated into the EHR and used during routine visits. Clinician usability and trust assessments will be administered at the end of each simulation period and again after the pilot phase.

The overall duration of participation for patients in the observational component is expected to be up to 24 months. Clinicians participating in the implementation evaluation will engage in shorter, structured sessions for simulation and a limited rollout period for the pilot.

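### Aim 3 adherence is compared across undefined study phases rather than within the randomised crossover, and trust in AIm-PBC is compared with a period in which the tool is not used

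*Protocol article*

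**What the plan says.** The Outcomes section states for Aim 3 that "the primary outcome will be the effectiveness and usability of the EHR-integrated CDS prototype", and then: "Effectiveness will be measured via improvements in clinician adherence to guideline-concordant care pathways". Adherence is therefore the effectiveness part of the primary outcome. The same paragraph also lists the System Usability Scale (SUS, target 70 or higher), the NASA-Task Load Index (NASA-TLX), an AI trust scale, decision accuracy and decision time.

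The Randomization section limits randomisation to the clinician-level simulation, with 1:1 allocation to "usual care followed by CDS-assisted care or CDS-assisted care followed by usual care", different cases in each period and a 1-week washout.

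The Statistical Analysis section assigns accuracy and time to paired t tests in that simulation and treats adherence differently. The join reads "tests within the randomized crossover simulation, whereas clinician adherence", and the sentence goes on to say that "clinician adherence to guideline-concordant care pathways will be evaluated using within-clinician comparisons across study phases".

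For the questionnaires, the same section says that SUS scores, "clinician trust scores from the AI trust scale adapted for AIm-PBC" and NASA-TLX scores "will be summarized and compared between CDS-assisted and usual care conditions". The Participant Timeline gives the schedule: "Clinician usability and trust assessments will be administered at the end of each simulation period and again after the pilot phase".

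**The concern.** There are two separate problems.

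**Adherence.** Randomisation is what allows a difference between conditions to be credited to the CDS tool. As worded, the adherence analysis stands outside the randomised comparison and rests on phases that differ in more than the presence of the tool: simulated cases versus live patients, a controlled session versus a clinic, and an earlier versus a later date. Making the comparison within clinicians removes stable differences between clinicians but none of these. The Hypothesis section expects better clinician adherence, so a central claim would rest on a confounded contrast although a randomised one is available.

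**Trust.** A scale adapted to one named tool needs that tool as its object. Usual care is set against CDS-assisted care, so by implication AIm-PBC is absent from it. A trust score from that period is then not a control value for a trust score given after using the tool.

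**Working it through.** The protocol states no power, effect size or SD for Aim 3, and the Recruitment section calls the 24 clinicians a pragmatic choice. There is no figure of the plan's to reproduce. The check is mainly a reading of the text, followed by an illustration of size.

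**Step 1: what study phases can mean.**
- The Study Design section and Table 1 make simulation phase 2 and real-world implementation phase 3.
- The Interventions section places simulation and pilot together in phase 3. Its phases 1 and 2 are model building, with no clinician decisions to compare. On that numbering a within-clinician comparison across phases would have nothing to compare.
- The two arms of the crossover are called periods or conditions (Randomization, Participant Timeline). The Results section uses phases for the simulation and the pilot.
- The contrast drawn in Statistical Analysis separates adherence from the crossover tests.

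Simulation versus pilot is therefore the most natural reading, though not the only one.

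**Step 2: what that comparison would estimate.** In the pilot the tool is in use at routine visits, and no usual-care arm is described.
- Pilot versus simulated usual care mixes the tool effect with the change from simulated to live care.
- Pilot versus simulated CDS-assisted care has the tool on both sides, so it is not a tool effect at all.

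**Step 3: illustration of size.** Inputs: n = 24 (Recruitment) and two-sided alpha 0.05 (Statistical Analysis). Assumptions: a paired t test for adherence (the protocol names none), no true tool effect, and a phase shift s in SDs of the within-clinician difference. The documents give no value for s.

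Across phases, all 24 clinicians carry the same shift, so the bias in the mean difference is s. The rejection rate comes from the noncentral t distribution with 23 df and noncentrality s × √24; for s = 0.3 this is 0.3 × 4.899 = 1.47.

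| Assumed phase shift s | False-positive rate |
|---|---|
| 0 | 5.0% |
| 0.1 | 7.6% |
| 0.2 | 15.6% |
| 0.3 | 29.1% |
| 0.5 | 65.0% |
| 0.8 | 96.3% |

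In a 12/12 crossover a period effect enters the CDS-minus-usual difference as +s in one sequence and −s in the other. Its contribution to the mean is (12s − 12s)/24 = 0. In 20,000 simulated trials per setting, without carryover:

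| Assumed period effect s | Plain paired t | Period-adjusted |
|---|---|---|
| 0 | 5.1% | 5.1% |
| 0.3 | 4.0% | 4.9% |
| 0.5 | 2.8% | 4.8% |
| 0.8 | 1.3% | 4.8% |

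The period term matters because the plain test becomes conservative as the period effect grows.

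**Step 4: can 24 clinicians carry the randomised comparison?** The standardised within-clinician difference detectable with 24 is 0.597 at 80% power and 0.691 at 90% (23 df). With a period term (22 df) it is 0.598 and 0.693. That is about 0.60 and 0.69 either way.

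**Step 5: trust under usual care.** With 1:1 allocation, 24 × 1/2 = 12 clinicians meet usual care first and score trust in AIm-PBC before using it in the simulation. The other 12 or so meet it second and score a tool last used before the 1-week washout. No clinician gives a usual-care trust score that refers to the period just completed.

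**The case against.** The best defence of the adherence wording is that study phases may loosely mean the crossover conditions. The Randomization section also says that primary comparisons are made within clinicians, which resembles the disputed sentence. This stands to the extent that the text is ambiguous, and it cannot be said for certain that adherence will not be compared between conditions. But the sentence would then still be wrong as written and need correcting.

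A second defence is that the Interventions section assigns real-world effectiveness to the pilot, so adherence in practice is the question of interest. That is fair, and it is a reason to keep pilot adherence in the report. It does not give the pilot a comparator.

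Three stronger readings are tempting, and the documents do not support them:
- **That the randomised comparison goes unused for Aim 3.** Decision accuracy and decision time are part of the Aim 3 outcomes and are tested within the crossover. Adherence is one component.
- **That the SUS comparison is as empty as the trust comparison.** Only the trust scale is described as adapted for AIm-PBC. The Harms section has simulation clinicians working with an EHR interface, so the SUS could rate the ordinary EHR under usual care. The gap is that the protocol does not say which system is rated, and its target of 70 is set for the prototype.
- **That an invalid trust test is planned.** The protocol speaks of summarising and comparing scores, and names a test only for accuracy and time.

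Usual care is not defined, and Figure 2 and the trust-scale appendix are not available here. The absence of AIm-PBC from usual care is therefore inferred, although the contrast with CDS-assisted care leaves little room for another reading.

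**Conclusion.** The point holds in two parts. First, the adherence comparison is undefined and, on its most natural reading, not randomised and confounded by setting, case type and time. A difference could not be attributed to the CDS tool. How far it would mislead depends on a phase shift that the documents do not give: over assumed shifts of 0.1 to 0.5 SD the false-positive rate runs from 7.6% to 65%. The crossover figures assume balanced sequences and no carryover; the design reduces carryover with separate cases and a washout but cannot exclude it. Second, the usual-care trust score has no proper object for any of the roughly 24 clinicians, so the trust contrast cannot be interpreted. This part rests on usual care not including AIm-PBC.

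The SUS needs only clarification. The NASA-TLX, accuracy and time comparisons are sound in both conditions. The Results section reports that recruitment has not begun, so both parts can be corrected in time.

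**What to change.** 1. **Adherence.** Score guideline-concordant actions on each simulated case. Make the CDS-assisted versus usual-care difference within the randomised crossover, with a period term, the comparative adherence analysis.
2. **Pilot.** Report pilot adherence descriptively, as real-world evidence that does not support a causal claim.
3. **Phases.** Use one phase numbering throughout, so that Table 1 and the Interventions section agree.
4. **Trust.** Collect the AI trust scale only after the CDS period and after the pilot, and report it as an estimate with a CI.
5. **SUS.** Either state that it rates the ordinary EHR interface under usual care, or report it for the CDS condition only. In both cases judge the target of 70 on the CDS score with its CI.
6. **Keep** the between-condition comparisons of NASA-TLX, decision accuracy and decision time.

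The cost is revised wording, a scoring key, and making sure that the simulated cases cover the pruritus, bone health and endoscopy-referral decisions, which the protocol does not yet state. One questionnaire is dropped from the usual-care period (two if the SUS is confined to the CDS condition). No extra clinicians are needed.
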